# STUDY POPULATION

## Population (base)

Participants will mainly be recruited from the obstetric wards at the Wilhelmina Children’s Hospital (WKZ) and Diakonessenhuis (Utrecht, the Netherlands).

As women who delivered without complications, may leave the hospital, we will approach these women who delivered at WKZ as well. This letter is added to the discharge letter/package in an envelope with a bright coloured label. The recruitment is further explained in paragraph 8.2. and depicted in the flowchart below:

[figure not shown]

The researchers will report to METC Utrecht the amount of parents that were not properly informed about the research by healthcare workers after contacting the first 50 mothers.

At the time an initiation visit will be planned, we will already send the informed consent and Patient Information Letter via e-mail.

## Inclusion criteria

In order to be eligible to participate in this study, a subject must meet all of the following criteria:

- All mother-child dyads that live in a proximity to Utrecht (because of logistical issues) and/or gave birth at the WKZ or Diakonessenhuis.
- Parents should have the intention to continue breastfeeding until at least 3 months postpartum.

## Exclusion criteria

A potential subject who meets any of the following criteria will be excluded from participation in this study:

- Concerning the child:
  - (inborn) severe cardiac or pulmonary disorders or other severe organ diseases
  - Extreme prematurity (defined as GA<32 weeks).
- Concerning parents:
  - Acquired or innate immune deficiencies (excluding asthma, eczema and allergies).
  - The (lactating) mother receives medication or has a physical condition which forms a contraindication for breastfeeding.
  - Insufficient control of the Dutch language (i.e. at least B1 level).

## Sample size calculation

## Study A:

A sample size of 1000 participants participants has an 80% power to detect a ratio of the means of 0.91 in those with vs. those without a medically attended LRTI using a two-sided two-sample t-test, assuming that 10% of the cohort participants have a medically attended LRTI (N=100) and that the 2’FL HMO concentration in the population has a mean of 3g/L, a standard deviation of 1g/L, and a normal distribution (Donovan2016). The significance level (alpha) is 0.05. The sample size was calculated using Power Analysis for Sample Size (PASS) 2008.

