## Replacement of individual subjects after withdrawal

A new mother-child dyad will be recruited to replace a withdrawn dyads when withdraw occurs before the first sample is taken.

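### As worded, Study A's inputs give about 73% power for a ratio of means of 0.91, not 80%; 80% power corresponds to a ratio of about 0.90

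*Protocol*

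**What the plan says.** The protocol's section 4.4 (Sample size calculation, Study A) gives the justification for N=1000 in one short paragraph. Its elements are:

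- Size: "A sample size of 1000 participants participants".
- Claim: "has an 80% power to detect a ratio of the means of 0.91 in those with vs. those without a medically attended LRTI".
- Test: "using a two-sided two-sample t-test", with alpha 0.05.
- Split: "assuming that 10% of the cohort participants have a medically attended LRTI (N=100"), which leaves 900 without.
- Exposure: the 2'FL "concentration in the population has a mean of 3g/L, a standard deviation of 1g/L, and a normal distribution".

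The paragraph gives one mean and one ratio. It does not give the two group means entered in the calculation, and it ties the 3 g/L to the population, not to either comparison group.

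**The concern.** A t-test is powered on a difference, so a ratio becomes a power figure only once the 3 g/L is assigned to a group or to the whole cohort. The wording assigns it to the whole cohort. Because 90% of the cohort is uninfected, taking it as the uninfected mean changes little. On both readings the stated inputs fall short of the stated 80%.

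This is the only power statement given for Study A. A reader who tries to reproduce it from the text will fail, and will take the study to be sensitive to a slightly smaller difference than it is.

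**Working it through.** **Inputs** (all from section 4.4, Study A): n1 = 100 with LRTI, n2 = 900 without, SD = 1 g/L, two-sided alpha = 0.05, ratio with/without = 0.91, mean 3 g/L.

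**Formulas.** SE = SD × √(1/n1 + 1/n2) = √(1/100 + 1/900) = 0.1054 g/L. Power ≈ Φ(difference/SE − 1.96). The results quoted use the exact noncentral t with 998 degrees of freedom, which differs from the normal approximation by about 0.1 point.

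**Step 1: reproducing the plan's figure.** Put 3 g/L in the LRTI group. The other mean is 3/0.91 = 3.297 and the difference is 0.297. Then 0.297/0.1054 = 2.815 and power is **80.3%**. The implied overall mean is 0.1 × 3 + 0.9 × 3.297 = 3.27 g/L, which is not the stated 3.

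**Step 2: the text as written.** Let 3 g/L be the overall mean. The mean without LRTI is 3/(0.9 + 0.1 × 0.91) = 3/0.991 = 3.027, and the mean with LRTI is 0.91 × 3.027 = 2.755. The difference is 0.2725, 0.2725/0.1054 = 2.585, and power is **73.3%**. If the SD of 1 is also read as the overall SD, the within-group SD is 0.997 and power is 73.6%.

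**Step 3: 3 g/L as the mean without LRTI.** The means are 3.00 and 2.73, the difference is 0.27, 0.27/0.1054 = 2.561, and power is **72.5%**.

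**Step 4: a log-scale test.** With CV 1/3, the log SD is √ln(1 + 1/9) = 0.3246 and −ln 0.91 = 0.0943. Power is **78.6%**.

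| Reading | Difference | Power at 0.91 |
|---|---|---|
| 3 g/L is the overall mean (as worded) | 0.2725 g/L | 73.3% |
| 3 g/L is the mean without LRTI | 0.27 g/L | 72.5% |
| 3 g/L is the mean with LRTI | 0.297 g/L | 80.3% |
| Log scale, CV 1/3 | 0.0943 (log) | 78.6% |

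**Step 5: what 80% power corresponds to.** At 100 vs 900 the difference detectable with 80% power is 0.2956 g/L. As a ratio this is:

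- (3 − 0.2956)/3 = 0.901 with 3 g/L as the mean without LRTI;
- 2.734/3.030 = 0.902 with 3 g/L as the overall mean;
- 3/3.2956 = 0.910 with 3 g/L as the mean with LRTI.

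**Step 6: rounding of the ratio.** Ratios from 0.905 to 0.9149 all print as 0.91. They give 77.1% down to 67.7% in step 3 and 77.8% down to 68.5% in step 2. None reaches 80%.

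**Step 7: equivalent sample size.** For scale only, 80% power at exactly 0.91 would take about 1180 participants (step 2) or 1200 (step 3).

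**The case against.** The strongest reply is that the 80% can be obtained from the printed numbers. Section 4.4 never says which mean was entered. Placing 3 g/L in the LRTI group gives 80.3%, and the 80%-power difference then rounds to a ratio of 0.91. That is probably how the figure arose, though this is an inference. A log-scale test is a second candidate. It would suit an effect stated as a ratio, and it reaches 80% at exp(−0.2956 × 0.3246) = 0.9085, which also rounds to 0.91.

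This stands to the extent that it would be wrong to call the 80% unobtainable, which a reader might infer from the 73%. It does not reconcile the text. The first route implies an overall mean of 3.27 g/L where the protocol gives 3, and the second conflicts with the stated normal distribution.

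A reader might also infer that losses reduce the power further, since section 5.4 limits replacement: "A new mother-child dyad will be recruited to replace a withdrawn dyads when withdraw occurs before the first sample is taken". The protocol does not support a figure for this. It states no loss rate, and section 7.4 plans to recover outcomes from general-practitioner data, with imputation where that fails. A dyad lost after its first sample can therefore still have both an exposure value and an outcome.

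**Conclusion.** The point holds as a modest correction. On the wording of section 4.4, power for a ratio of 0.91 is about 73% (72.5% to 73.3%). With N=1000, 80% power corresponds to a ratio of about 0.90, a difference of 0.296 g/L. This rests only on the protocol's own inputs: 100 vs 900, SD 1 g/L, normality, a two-sided t-test at 0.05, and 3 g/L read as the overall mean or as that of the uninfected majority.

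Two stronger conclusions do not follow. First, 27% is not the type II error of the primary result. Section 7.1 plans an adjusted Poisson regression of the number of infections on 2'FL, whereas the 73% belongs to an unadjusted t-test on LRTI status. Second, nothing here shows that 1000 is too few. The protocol does not argue that 0.91, as opposed to 0.90, is the difference that must be detected.

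**What to change.** Keep N=1000. In section 4.4, state both assumed group means and the scale on which the test was done, and then make the sentence agree with them:

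- If 3 g/L is the population mean, say that 100 vs 900 gives 80% power for a ratio of about 0.90 (means about 2.73 and 3.03 g/L), or about 73% power for 0.91.
- If 3 g/L was meant as the mean of infants with LRTI, keep 80% and 0.91, give the means as 3.00 and 3.30 g/L, and correct the description that attaches 3 g/L to the population.
- If the test was on the log scale, say so, and replace the normal assumption with the one used.

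The sponsor can settle which applies from the saved input of the original calculation. The cost is one or two sentences, with no change to recruitment, procedures or analysis. In the first case the stated detectable effect becomes slightly less favourable.

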# METHODS

## Study parameters/endpoints

### Main study parameter/endpoint

- Parent-reported medically attended respiratory tract infection during the first year of life.

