## Primary study parameter(s)

## The association between 2’FL concentrations and the number of medically attended respiratory tract infections during the first year of life will be determined using Poisson regression analysis, adjusted for potential confounders. Potential confounders will be identified by a literature search, complemented by expert knowledge. One such potential confounder is like 3’SL that is both suggested to exert a direct antiviral effect as well as to be associated with a shorter lactation duration (Azad201,; Laucirica2017, Pandey2018).

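### The 80% power for Study A belongs to an unadjusted t-test on yes/no LRTI, not to the primary analysis, which is an adjusted Poisson regression of the MARI count

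*Protocol*

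**What the plan says.** Protocol section 4.4 (Study A) claims 80% power for 1000 mother-child pairs. The target effect is "a ratio of the means of 0.91 in those with vs. those without a medically attended LRTI". Section 4.4 says that this figure was obtained "using a two-sided two-sample t-test, assuming that 10% of the cohort participants have a medically attended LRTI (N=100" infants). Concentration of 2'FL is taken as normal with a population mean of 3 g/L and SD of 1 g/L; alpha is 0.05.

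Protocol section 5.1.1 names the main endpoint: "Parent-reported medically attended respiratory tract infection during the first year of life". The Summary for Study A says that this is the number of such infections over the year.

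Protocol section 7.1 plans the primary analysis, which relates 2'FL to the infection count: "number of medically attended respiratory tract infections during the first year of life will be determined using Poisson regression analysis". The model is to include confounders. Another milk oligosaccharide, 3'SL, is given as an example.

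LRTI as a study outcome appears only in section 4.4. Sections 5.1.1 and 5.1.2 do not list it, and sections 7.1 and 7.2 plan no t-test for Study A.

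**The concern.** The sizing and the primary analysis differ in four respects:

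- **Outcome:** lower respiratory tract infection against any respiratory tract infection.
- **Scale:** yes/no against a count.
- **Effect measure:** a ratio of mean 2'FL concentrations against a rate ratio.
- **Model:** an unadjusted comparison against a regression adjusted for confounders.

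No sentence connects the two. The protocol gives no expected MARI rate, no target rate ratio, no allowance for overdispersion and no correlation between 2'FL and the confounders. A reader who takes the 80% as the power of the primary analysis is relying on a figure calculated for something else, and the protocol does not say what rate ratio the primary analysis can detect. A statistical analysis plan may exist, but the power figure stands in the protocol, and the protocol's own endpoint and analysis sections disagree with it.

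**Working it through.** **1. The stated figure.** Inputs from section 4.4: 100 infants with LRTI and 900 without, SD 1 g/L, ratio 0.91, two-sided alpha 0.05.

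SE = √(1/100 + 1/900) = 0.1054. Power ≈ Φ(δ/SE − 1.96).

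| Reading of 3 g/L | δ (g/L) | Power |
|---|---|---|
| Mean without LRTI | 3 × 0.09 = 0.27 | 73% |
| Mean of the population (as worded) | 0.09 × 3/0.991 = 0.2725 | 73% |
| Mean with LRTI | 3/0.91 − 3 = 0.297 | 80% |

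The exact noncentral t gives 72.5%, 73.3% and 80.3%. A test on the log scale with coefficient of variation 1/3 gives 78.6%, but the protocol assumes a normal distribution. On the literal reading, 80% power needs δ = 2.80 × 0.1054 = 0.295 g/L, a ratio of about 0.90.

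**2. An equivalent effect for the planned model.** For two normal groups with SD 1 that differ by 0.27, the log odds ratio is −0.27 per g/L. Taken as a log rate ratio, this gives exp(−0.27) = 0.76 per g/L. Carrying it from LRTI to all MARIs is an assumption.

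**3. Power of the planned model.** With mean count μ, dispersion φ, and R² for 2'FL on the confounders:

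Power ≈ Φ(0.27 × √(N μ (1 − R²)/φ) − 1.96), N = 1000.

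If 10% of infants have at least one event, Poisson counts imply μ = −ln(0.9) = 0.105. The larger means are illustrative.

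| μ | R² 0, φ 1 | R² 0.2, φ 1 | R² 0.2, φ 1.5 | R² 0.3, φ 2 |
|---|---|---|---|---|
| 0.105 | 79% | 70% | 52% | 37% |
| 0.2 | 97% | 93% | 80% | 62% |
| 0.3 | >99% | 99% | 93% | 79% |
| 0.5 | >99% | >99% | 99% | 95% |
| 1.0 | >99% | >99% | >99% | >99% |

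Two entries worked out: at μ 0.105, R² 0, φ 1, Φ(0.27 × √105 − 1.96) = Φ(0.81) = 79%; at μ 0.105, R² 0.3, φ 2, Φ(0.27 × √36.75 − 1.96) = Φ(−0.32) = 37%. Simulation at μ 0.105 without overdispersion (1000 runs, robust variance) gave 78% unadjusted and 68% adjusted with R² about 0.2.

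**4. Rate ratio per 1 g/L detectable with 80% power**, exp(−2.80/√(N μ (1 − R²)/φ)):

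| μ | R² 0, φ 1 | R² 0.2, φ 1 | R² 0.2, φ 1.5 | R² 0.3, φ 2 |
|---|---|---|---|---|
| 0.105 | 0.761 | 0.737 | 0.688 | 0.630 |
| 0.2 | 0.820 | 0.801 | 0.762 | 0.715 |
| 0.3 | 0.851 | 0.835 | 0.801 | 0.761 |
| 0.5 | 0.882 | 0.869 | 0.842 | 0.809 |
| 1.0 | 0.915 | 0.906 | 0.886 | 0.861 |

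**5. How far the 37% can be pressed.** If the counts are negative binomial with φ = 2, a mean of 0.105 implies 1 − 2^(−0.105) = 7% of infants affected, below the protocol's 10%. Holding 10% gives μ = 0.105/ln 2 = 0.152, and power at R² 0.3 is then Φ(0.27 × √53.2 − 1.96) = 50%. The 37% is therefore an extreme corner.

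**The case against.** The strongest reply is that comparing mean exposure between infants with and without an event is a close stand-in for regressing that event on exposure. This stands: at a mean count of 0.105, unadjusted Poisson power is 79%, so the choice of a t-test alone costs almost nothing. What remains is the change of outcome and the adjustment, and the protocol bridges neither.

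A second reply is that every medically attended LRTI is also a MARI, so MARIs cannot be rarer than the LRTIs assumed, and the primary analysis may have more than 80% power. This also stands as a possibility. At mean counts of 0.3 and above, the detectable rate ratios in the working lie at or closer to 1 than 0.76. It does not rescue the stated figure, because the protocol gives no MARI rate and does not claim the same effect on all respiratory infections as on LRTI.

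A reader might infer that the study is too small. The documents do not support that, since the result depends on rates they do not give. A reader might also infer room to switch outcomes later. That is speculation: the objectives, the endpoint section and the analysis section all name medically attended respiratory tract infection. Nor would a null result be uninterpretable, because a confidence interval for the rate ratio can still be read.

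**Conclusion.** The point holds as a mismatch between the power statement and the primary analysis. The 80% in section 4.4 describes a different outcome and an unadjusted test, and it does not carry over in either direction. At an assumed rate ratio of 0.76 per g/L, power of the planned model runs from about 37% in the extreme corner at a mean count of 0.105 to nearly 100% at a mean of 1.0. The position in that range depends on the mean MARI count, dispersion and confounder R², none of which the protocol states. No shortfall in sample size is shown.

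The stated figure also fails on its own terms as worded: about 73% with 3 g/L as the population mean, and about 80% only if 3 g/L is the mean of the LRTI group. This second finding rests only on inputs in section 4.4.

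**What to change.** In section 4.4, keep N at 1000 and replace the Study A statement with the rate ratio per 1 g/L of 2'FL detectable with 80% power in the adjusted Poisson model for the MARI count. Give it over a stated range of mean count, overdispersion and confounder R², with the source of each.

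If the t-test is kept, label it an approximation, reconcile LRTI with MARI, and correct either the power (about 73% at a ratio of 0.91) or the ratio (about 0.90 for 80%), saying which group or population has the mean of 3 g/L.

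The cost is one paragraph and possibly a less favourable stated figure. Recruitment, endpoint and analysis model stay as they are.

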**Study B: .**

Group sample sizes of 9 and 9 achieve 82% power to detect a difference of 88.3 between the null hypothesis that both group means are 100.7 and the alternative hypothesis that the mean of group 2 is 12.4 with estimated group standard deviations of 80.0 and 18.0 and with a significance level (alpha) of 0.05 using a two-sided two-sample t-test (Maertens2016).

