There is a growing interest in the use of maternal vaccinations during pregnancy and several maternal vaccinations are at this moment studied, e.g. against Bordetella pertussis, influenza, group B streptococcus and RSV (Marchant2017, Abu Raya2017, Heath2017) ). Already, a maternal vaccination against Bordetella pertussis is approved for vaccination during pregnancy and is currently implemented in the UK (Amirthalingam2016). From December 2019 onwards, all pregnant women in the Netherlands will be offered a Bordetella pertussis vaccination at 28 till 32 weeks gestational age (Rijksoverheid). Although it is generally believed that the protective effect of maternal vaccination is derived from placental transfer of antibodies, definitive evidence whether placental transfer or transfer of immunity through breastfeeding or amniotic fluid is absent (Marchant2017, Pou2019). Moreover, maternal vaccination studies in mice demonstrated that transfer of antibodies through breastfeeding and not placental transfer is of major importance to protect offspring (Gaillard2017,Caballero-Flores2019). Further mechanistic insights into maternal immunity transfer will be essential for further development of maternal vaccinations. Therefore we plan to perform a substudy (afterwards called study B) within the PRIMA human milk cohort. In this cohort (n=20) we will collect additional samples next to the breastfeeding samples and the questionnaires. We will sample cord blood, amniotic fluid, maternal blood sample and saliva samples of the participating children. Cord blood samples and the amniotic fluid samples will be compared to the composition of antibodies and HMOS in human milk, as it is known they contain HMOs and/or antibodies as well (Jacobino2016, Hirschmugl2019). The maternal blood samples will be used to observe the maternal response to Bordetella pertussis revaccination. Likewise, the maternal blood sample will serve as a golden standard to see if there is any kind of selection of antibody transfer through one of the three media (i.e. cord blood, human milk or amniotic fluid).

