**Study B:**

In the sub study we will also collect additional samples to research what the influence of breastfeeding is on immune development, compared to other routes that are enrolled in the transfer of maternal immunity to the neonate. This will be done in a subgroup of 20 mother-child dyads. The samples that we will collect are cord blood samples, a maternal blood sample and an amniotic fluid sample. Jacobino et al. showed that antibodies retrieved form human amniotic fluid protected mice pups against RSV-infections (Jacobino2016). Very little is known about the protective value antibody titters in cord blood. Active placental transport of maternal antibodies to the neonatal blood has been described, but little is known about the effectiveness of these antibodies (Kohler1966). To obtain more insight in the effect of the antibodies that are being transferred by breastfeeding, we will compare the effect of breastfeeding to the antibodies in cord blood and amniotic fluid. To evaluate the effect of the maternal Bordetella pertussis vaccination on (pertussis-specific) immune development in children, we will also collect saliva samples at 1 week, 1 month, 3 months, 6 months and 12 months postpartum. Saliva samples offer an ideal method to evaluate the (Bordetella-pertussis specific) immune development during the first year of life since saliva antibody titters correlate well with serum titters but saliva samples are considered to be non-invasive.

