**Study B:**

Secondary objective 5:

To describe antibody concentrations in compartments relevant to materno-fetal antibody transfer. We will define the association between maternal serum, breast milk antibodies, cord blood, amniotic and infant antibodies over time. This study is performed while maternal pertussis vaccination is introduced. We will therefore analyse total and pertussis-specific antibody concentrations.

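### Study B's 82% power belongs to an unnamed 9 versus 9 comparison that the design does not secure, and not to its section 2 objective

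*Protocol*

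**What the plan says.** Section 4.4 (Study B) states: "Group sample sizes of 9 and 9 achieve 82% power to detect a difference of 88.3". The inputs are "the null hypothesis that both group means are 100.7", "the alternative hypothesis that the mean of group 2 is 12.4", "estimated group standard deviations of 80.0 and 18.0" and "a significance level (alpha) of 0.05 using a two-sided two-sample t-test". No group, analyte, compartment or unit is named. The planning values come from a cited source whose title describes a controlled cohort study of pertussis vaccination in pregnancy.

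Other parts of the protocol that bear on this:

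- The Summary and section 1 describe Study B as one subgroup of 20 mother-child dyads, and the Summary has them recruited during pregnancy.
- Sections 4.2 and 4.3 contain no criterion on maternal vaccination. Section 5.1.3 lists the mother's vaccination status among the other parameters to be recorded.
- The Summary's rationale for Study B says: "From December 2019 onwards, all pregnant women in the Netherlands will be offered a Bordetella pertussis vaccination at 28 till 32 weeks gestational age".
- The Study B objective in section 2 is to describe antibody concentrations by compartment, and adds: "We will define the association between maternal serum, breast milk antibodies, cord blood, amniotic and infant antibodies over time". It notes that the study runs while the vaccination programme is being introduced.
- Section 1 gives the purpose of the infant saliva samples as: "To evaluate the effect of the maternal Bordetella pertussis vaccination on (pertussis-specific) immune development in children". The Summary also says that maternal blood will show the mother's response to revaccination.
- Maternal blood is collected in the first week postpartum (Summary), preferably at the first house visit (section 5.2).

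**The concern.** A two-sample t-test needs two independent groups. Study B as described has one group, and its section 2 objective concerns several measurements within the same dyads, which a two-group test of means does not address. The only number offered to justify the size of Study B is therefore tied to a comparison that no other part of the protocol sets up.

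Two things are at stake. The section 2 objective has no size justification of its own. And the stated aim of evaluating an effect of maternal vaccination needs unvaccinated dyads, whose number is left to chance. An analysis plan could add a split by recorded status, but it cannot supply dyads that were not recruited.

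**Working it through.** **1. The plan's own figure.** Inputs from section 4.4: n = 9 and 9, difference 100.7 − 12.4 = 88.3, SDs 80.0 and 18.0, two-sided alpha 0.05.

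- SE = √(80²/9 + 18²/9) = √(711.1 + 36.0) = 27.33
- Satterthwaite df = 747.1² / (711.1²/8 + 36.0²/8) = 8.81
- Noncentrality = 88.3 / 27.33 = 3.23
- Power from the noncentral t = 81.7% (81.8% by simulation)

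The equal-variance t-test (df 16) gives 85.8%, so the stated 82% is the Welch version. The figure reproduces.

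**2. What the two groups could be.**

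- *Vaccinated and unvaccinated mothers.* This fits the title of the cited source and the pertussis rationale, but the protocol does not say so. Eligibility, recruitment and the description of the subgroup contain nothing that produces two such groups.
- *Two compartments of the same dyads.* The observations would then be paired, and an independent-samples test would not apply.

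Under either reading, section 4.4 does not match the rest of the protocol.

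**3. Is 9 per group necessary?** Assume that group 1 (mean 100.7, SD 80) is vaccinated, and apply the Welch calculation to other splits of 20. For 16/4: SE = √(6400/16 + 324/4) = √481 = 21.93, df 18.0, noncentrality 4.03.

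| Vaccinated / unvaccinated | Welch power, raw scale |
|---|---|
| 12 / 8 | 92% |
| 14 / 6 | 96% |
| 16 / 4 | 97% |
| 17 / 3 | 96% |
| 18 / 2 | 92% by formula, 86% by simulation |
| 19 / 1 or 20 / 0 | not estimable |

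Power rises because most of the variance sits in the larger group. Two limits apply. The equal-variance test falls to 53% at 16/4 (56% by simulation). For log-normal data with the same means and SDs (log variance = ln(1 + SD²/mean²)), log-scale Welch power is over 99% at 9/9, about 86% at 16/4 and 61% to 62% at 17/3. A workable minimum is thus about 3 unvaccinated dyads on the raw scale and about 4 on the log scale.

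**4. Chance of reaching that minimum.** The protocol gives no uptake, so uptake u is assumed. With 20 unselected dyads, the number unvaccinated is X ~ Binomial(20, 1 − u).

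| Assumed uptake | Expected unvaccinated | P(X ≥ 3) | P(X ≥ 4) |
|---|---|---|---|
| 70% | 6 | 96% | 89% |
| 80% | 4 | 79% | 59% |
| 90% | 2 | 32% | 13% |
| 95% | 1 | 8% | 2% |

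At 95% uptake, the chance of at most one unvaccinated dyad is 74%.

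**5. What 20 dyads give for the section 2 objective.** For a correlation r between two compartments, Fisher's z = atanh(r) has SE 1/√(20 − 3) = 0.2425.

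- r = 0.5: z = 0.549 ± 1.96 × 0.2425, that is 0.074 to 1.025. Back-transformed, the 95% CI is 0.07 to 0.77.
- r = 0.7: 95% CI 0.37 to 0.87.
- Smallest r with 80% power: tanh((1.960 + 0.842) × 0.2425) = 0.59. Power at r = 0.5 is 62%.

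**The case against.** The strongest reply is that the calculation serves one of several stated aims. The rationale speaks of a vaccination effect, vaccination status is recorded, an offer to all is not universal uptake, and section 2 places the study in the period of introduction, when a mixed cohort is plausible. A split by status may be planned in an analysis plan that is not shown, and the design figure and recruitment flowchart are not available here. Study B is also a small substudy on which the primary objective does not depend.

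Much of this stands. A comparison group may well arise, and the consequence is confined to Study B. What it does not answer is that section 4.4 names neither the groups nor the aim it supports, that nothing in the text secures a second group, and that the section 2 objective has no size justification.

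A reader might infer three stronger points, none of which the documents support:

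- *That at least 9 unvaccinated dyads are needed.* On that threshold the chance would be only 11% at 70% uptake and 1% at 80%. Step 3 shows that the stated inputs do not require 9.
- *That Study B is underpowered because SD 18.0 exceeds mean 12.4.* A normal model would put about 25% of group 2 below zero, so it is a poor description of a concentration. But log-normal simulation at 9/9 gives 95% power on the raw scale and over 99% on the log scale. The choice of scale may be left to the analysis plan.
- *That Study B will have no unvaccinated mothers.* The protocol gives no uptake figure and does not say how many dyads are recruited before or after the offer begins.

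**Conclusion.** The concern holds in limited form. The 82% is correctly calculated, but it belongs to a comparison that the protocol neither defines nor secures, and it does not bear on the association objective in section 2. For that objective, 20 dyads give wide intervals and 80% power only for correlations of about 0.59 or more.

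If the contrast is vaccinated versus unvaccinated, the risk of having no usable comparison is small at 70% uptake, moderate at 80% and serious at 90% or above. This rests on three assumptions: the identity of the groups (inferred from a reference title), the SD-80 group being the vaccinated one, and the uptake values. The fault in section 4.4 itself depends on none of them.

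A related wording point is that a single maternal sample after delivery shows a level. It cannot by itself show a response to revaccination.

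**What to change.** In section 4.4, remove the 9 versus 9 calculation as the justification for Study B. Label Study B descriptive and state what 20 dyads deliver for the section 2 objective, for example the interval of 0.07 to 0.77 for a correlation of 0.5 and the detectable correlation of about 0.59. In the Summary and section 1, limit the wording on the effect of vaccination and the response to revaccination to what one postpartum maternal sample without an assured comparator can show. This costs wording only, and 20 dyads can stay.

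If the sponsor keeps the contrast, section 4.4 should name the groups, analyte and compartment. It should state the power for the split expected among 20 dyads, with the assumed uptake and the analysis scale. It should also give the minimum number of unvaccinated dyads below which the comparison will not be made. A quota of 9 per group is not needed. The cost is a stated uptake assumption and acceptance that the comparison may be dropped.
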